#### Oxygen consumption

During ISWT, a comprehensive analysis of physiological responses will be conducted using the portable PNOĒ telemetry system (ENDO Medical, Palo Alto, CA). This system enables the assessment of variables like oxygen consumption (VO_2_) and carbon dioxide (VCO_2_) production through a breath-by-breath approach [23].

#### Muscle oxygenation

Employing the PortaMon spectrometer (Artinis Medical, Netherlands), alterations in oxyhemoglobin (O_2_Hb) and deoxyhemoglobin (HHb) chromophore concentrations will serve as indicators for assessing blood volume and oxygen consumption in the lower limb muscles. For this purpose, an optode will be affixed to the skin using adhesive tape and then covered with black tissue over the proximal third of the vastus lateralis muscle on the dominant limb. Throughout the ISWT protocol, the concentrations of O_2_Hb and HHb will be continuously monitored within the muscle [24, 25].

### Phase 2: Evaluation of the gamified application for prescription and physical training in a controlled environment

Phase 2 will entail a comprehensive examination of the gamified application’s effectiveness within a controlled laboratory setting. Assessments and interventions during this phase will be closely supervised by researchers. The functional test conducted during phase 1 will be replicated at both the outset and the conclusion of phase 2, with trained researchers overseeing the process.

#### Prescription of physical exercise

Building upon the ISWT results, the intensity of physical exercise will be tailored. The training protocol will span six weeks, with sessions conducted 5 days a week. The training volume will encompass a minimum of 300 min weekly at moderate intensity (40–60% of heart rate reserve) or a minimum of 150 min weekly at vigorous intensity (60–80% of heart rate reserve) [26]. The training will involve a one-step staircase (20 cm height, 60 cm length, and 40 cm width). The target intensity will range from 40 to 80% of the heart rate reserve, calculated based on ISWT. The heart rate reserve will be determined by subtracting the resting heart rate from the maximum heart rate achieved during the functional test. Throughout the exercise session, both HR monitors (Polar H10) and the test biosensor will be closely monitored.

The gamified smartphone application will offer visual feedback on intensity and heart rate, alongside researcher observation of heart rate measured by Polar H10 and the biosensor linked to the gamified application. Additionally, the biosensor, equipped with an accelerometer, will track step count during training. Phases within the scenario will be defined using gamification techniques, incorporating rewards, competitions, and other strategies to ensure adherence and engagement across varying intensities, including warm-up, maintenance, and cool-down phases.

In the initial week, sessions will last 30 min: a 5-min stationary gait warm-up, 20 min of step interval training (2 min at target HR and 3 min at low intensity), and a 5-min stationary gait cool-down. Over the subsequent 5 weeks, each session will extend to 60 min: a 5-min stationary gait warm-up, 50 min of step training at target HR, and a 5-min stationary gait cool-down. Sessions will occur at least twice a week and no more than five times. To meet the minimum adherence criterion, participants must achieve at least 70% of the prescribed training volume outlined in the protocol. Upon completing the 6-week training program, a new functional capacity assessment will be conducted.

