**Methods:**

This exploratory study, followed by a noninferiority, investigator-blinded randomized clinical trial, will be divided into three phases: (1) development and validation of a sensor for real-time biofeedback during a functional assessment test; (2) integration of biofeedback and gamification into an app for the structured prescription of physical training within a controlled setting; and (3) implementation of biofeedback and gamification into an app for the prescription and monitoring of physical training in an uncontrolled setting. Phase 1 entails a validation test of a biosensor—monitoring heart rate (HR) and steps—during a modified shuttle walk test. In phase 2, the biosensor interfaces with a gamified smartphone application. The training regimen spans 6 weeks, 5 days weekly, with each session lasting 60 min: a five-min warm-up involving stationary gait, followed by 50 min of training at the target HR on the step and concluding with a five-min cool-down at a stationary pace. After 6 weeks of training, a new functional capacity test is conducted. Phase 3 involves an investigator-blinded, randomized clinical trial to demonstrate noninferiority. Participants are randomly assigned to either the intervention group (IG) or the control group (CG). IG participants practice exercise using the gamified application in an uncontrolled environment according to the prescribed method outlined in phase 2. CG participants receive PA practice guidelines exclusively.

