For phase 3, a qualitative analysis will be performed on participants’ diary reports and a quantitative assessment of potential gamified application failures. Step count measured by the biosensor will be compared to the ActiGraph accelerometer using Student’s *t*-test or Wilcoxon rank-sum test, depending on residual distribution. Agreement between step counts will be evaluated using Bland–Altman test, Lin’s correlation coefficient, and intraclass correlation coefficient. Pre- and post-exercise protocol data, encompassing functional capacity, VO_2_, tissue oxygenation, maximum and resting HR, systemic blood pressure, subjective exertion perception, endothelial function, and HRV, will be analysed using Student’s *t*-test for paired samples or Wilcoxon signed-rank test, aligned with residual distribution. Participants achieving a minimum of 70% completion of the prescribed protocol will be classified as adherent. As the random allocation is anticipated to ensure baseline comparability between the control and intervention groups, unadjusted analyses will primarily be carried out. In the event of any non-comparability in baseline characteristics due to chance, appropriate adjustments will be made to prevent potential biases. Significance level will be set at *p* < 0.05. The data will be analysed using Statistical Package for the Social Sciences (SPSS) 20.0 (SPSS, Chicago, IL, USA).

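### The 70% adherence rule rests on a prescribed exercise volume that the protocol states in ways that do not agree

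*Protocol article*

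**What the plan says.** All of the conflicting statements about frequency and volume stand in one section of the protocol article, Prescription of physical exercise (phase 2):

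- Frequency, first statement: "The training protocol will span six weeks, with sessions conducted 5 days a week".
- Volume: "The training volume will encompass a minimum of 300 min weekly at moderate intensity", or as the alternative 150 min weekly at vigorous intensity.
- Session length: 30 min in week 1, of which 20 min is interval stepping (2 min at target heart rate, then 3 min at low intensity). In weeks 2 to 6 it is 60 min, of which 50 min is at target heart rate.
- Frequency, second statement: "Sessions will occur at least twice a week and no more than five times".
- Adherence, in the next sentence: "participants must achieve at least 70% of the prescribed training volume outlined in the protocol".

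The phase 3 section carries this regimen over to the intervention group (IG). It gives the control group (CG) the same 300 or 150 min weekly target, self-assessed, with no session schedule. Statistical methods {20a} restates the rule for phase 3: "Participants achieving a minimum of 70% completion of the prescribed protocol will be classified as adherent". The abstract has no shorter first week: "The training regimen spans 6 weeks, 5 days weekly, with each session lasting 60 min".

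Outcomes {12} lists the between-group comparison of adherence among the primary outcomes. Sample size {14} is built on adherence of 70% in the IG and 50% in the CG. The phase 3 benchmark in {20a} is also expressed as adherence.

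**The concern.** A 70% rule needs a defined 100%. Both statements of the rule point back to the protocol's own prescription, and that prescription gives a fixed five-session week, a range of two to five sessions, and weekly minima that the lower end of the range cannot reach. An analysis plan could not settle this by elaboration; it would have to choose between conflicting sentences.

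If the choice is left until the phase 3 data are in hand, it decides who counts as adherent on a primary outcome. Someone who attends at a frequency the protocol expressly allows can be classed as a failure under one sentence and a success under another.

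**Working it through.** **The plan's own figure.** For 70% vs 50%, two-sided 5%, 80% power, 1:1, the usual two-proportion formula gives 93 per group, or 103 with continuity correction; the protocol has 104. Allowing for 30% loss, 104 / 0.70 = 148.6, that is 149 per group and 298 in total, as stated. The sample size arithmetic is not in question here.

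**Six-week volumes.** With s sessions a week, whole-session minutes are s × 30 (week 1) + 5 × s × 60 (weeks 2 to 6) = 330s.

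| Reading of the prescription | Six-week volume | 70% cut-off |
|---|---|---|
| Five sessions a week | 330 × 5 = 1,650 min | 1,155 min |
| 300 min a week | 6 × 300 = 1,800 min | 1,260 min |
| Two sessions a week (lower limit) | 330 × 2 = 660 min | 462 min |

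The abstract's version, 30 × 60 = 1,800 min, differs from the 1,650 min of the detailed schedule because it leaves out the 30-min first week.

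**Do the statements agree?**

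- Two 60-min sessions: 2 × 60 = 120 min a week, below both 300 and 150.
- Week 1 at full attendance: 5 × 30 = 150 min, half of the moderate minimum.
- Weeks 2 to 6 at full attendance: 5 × 60 = 300 min if whole sessions count, but 5 × 50 = 250 min if only time at target counts.

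**Does the classification change?** All sessions completed at a constant weekly frequency, whole-session minutes:

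| Sessions a week | Minutes | % of 1,650 | % of 1,800 | % of 660 |
|---|---|---|---|---|
| 2 | 660 | 40.0 | 36.7 | 100 |
| 3 | 990 | 60.0 | 55.0 | 150 |
| 4 | 1,320 | 80.0 | 73.3 | 200 |

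At two or three sessions a week the participant keeps to the stated frequency and fails 70% on the first two denominators, but passes on the third. At four a week the three agree.

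**Fewest sessions, out of 30, that can reach 70%:**

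- Sessions counted: 0.70 × 30 = 21.
- Whole-session minutes against 1,650: 19 × 60 = 1,140 < 1,155 and 20 × 60 = 1,200, so 20.
- Whole-session minutes against 1,800: 21 × 60 = 1,260, so 21.
- Minutes at target against 1,800: all 25 long sessions give 25 × 50 = 1,250, short of 1,260. Taking the 20 min of week-1 stepping as four 2 + 3 min cycles (an assumption), each week-1 session adds 8 min, so two are needed: 1,266 min, 27 sessions. If all 20 min count, one is enough: 1,270 min, 26 sessions. Full attendance then yields only 1,290 to 1,350 min, or 72% to 75% of 1,800.

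**The case against.** The best defence is that the text does point to a denominator. The only other place that speaks of training volume is the sentence setting 300 or 150 min weekly, and the control group has the same figures. Five 60-min sessions are exactly 300 min, which suggests that whole sessions count. The range of two to five could then be a tolerance on weekly attendance around a five-day prescription. On that reading both arms share a bar, and the whole-session readings differ by a single session (20 or 21).

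Much of this stands, and it rules out several stronger inferences:

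- *The arms are held to different bars.* A reader might infer this from the session regimen in one arm and the minutes target in the other. It follows only if the IG is scored on sessions, which no section says. If 300 or 150 min is the denominator, the arms share it.
- *The cut-off runs from 11 to 27 sessions.* The low end, 11 to 13, comes from 70% of 6 × 150 = 900 min, that is 630 min (whole sessions or time at target). It belongs to the vigorous alternative only and is not a rival cut-off for someone training at moderate intensity. The high end needs time at target alone to count.
- *300 and 150 contradict each other.* They do not; they are alternatives by intensity.
- *The abstract is a separate error.* Leaving out the first-week ramp is ordinary condensation, though it should be aligned.

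The defence does not remove the conflict. The text does not call the lower limit of two sessions a tolerance. Even if it is one, a participant at that limit reaches 40% of the five-day schedule and 120 min a week from week 2, under both minima. The phase 3 rule speaks of the prescribed protocol, not of volume, and the IG's prescribed protocol is the session regimen. The target intensity spans 40% to 80% of heart rate reserve, so both minima are in play, and nothing says which one a given participant is scored against.

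**Conclusion.** The point holds in a limited form. The frequency and volume statements in Prescription of physical exercise contradict one another, and the adherence rule rests on them without naming the volume that counts as 100%.

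The effect is greatest for participants at two or three sessions a week, who meet the stated frequency but score 40% or 60% of the five-day schedule. Among whole-session readings against five days or 300 min a week it is small, a minimum of 20 to 21 sessions. The unstated counting rule matters more: with time at target alone against 300 min a week, the minimum is 26 to 27 of 30. These figures assume completed sessions of the stated length and, for the figure of 27, four interval cycles in each week-1 session.

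Adherence is one of five listed primary outcomes, but it is the one that drives the sample size and the phase 3 benchmark, so its definition should not be left open. Whether the arms face different bars depends on the reading chosen; the documents do not establish that they do. The figures of 104 and 149 per group are unaffected.

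**What to change.** The investigators should reconcile the frequency and volume statements in Prescription of physical exercise and in the phase 3 section, and align the abstract with the result. Which schedule or volume is right is theirs to decide.

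Before phase 3 data are seen, the protocol should then state, keeping the 70% threshold:

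- one adherence denominator and one unit, applied identically to both arms;
- whether warm-up, cool-down and the low-intensity intervals of week 1 count;
- how the intensity-dependent 300 or 150 min target is applied to a participant, including one whose intensity varies.

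The wording in {20a} should refer to that single definition. The cost is a formal protocol revision, wording only, with no change to the sample size calculation. The control group's weekly record must be able to supply the chosen unit; if it cannot, the recording sheet needs a matching change.

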#### Gamified application implementation

A mobile platform integrating gamification techniques will be deployed to ensure adherence to prescribed physical activity (PA) regimens, promoting user engagement. To select the most suitable platform, an analysis will be conducted of prevalent devices among the Brazilian population, as identified in PGB 2021 [27].

This system will enable the design of physical activities that ensure adherence, exercise intensity, and duration. Requirements will be categorized into functional and non-functional aspects. Functional requirements define the system’s functions and responses to specific inputs and behaviours, while non-functional requirements outline quality standards and limitations on system services.

The development tools chosen for this system are Blender 2.91 [28] for creating models, animations, and textures and Unity 2020 [29] for animation, direction, rendering, and programming. These tools were selected due to their extensive use in similar solutions.

Avatars will reflect individual physical characteristics, including factors like body fat levels, which directly impact the avatar’s appearance. Hair and facial hair customization will be offered with 15 distinct options for each. Additionally, the virtual store within the system will provide 15 clothing models for both genders.

Creating the scenarios involves compiling visual reference materials and adjusting scene elements to match common smartphone screen dimensions. Decoration pieces will be modelled for in-game scenarios and can be purchased using earned in-game coins obtained through exercising. An original soundtrack and synthesized sound effects will enhance the gaming experience, aligning with the game’s artistic direction.

All interactions between characters and scenario items will be programmed, encompassing actions like sleeping, eating, and exercising on various equipment like treadmills and bicycles. Engaging mini-games will be integrated into equipment-based exercises, offering players points redeemable for in-game store items. To engage in exercises, players will expend energy points earned through real-world physical activity.

### Phase 3: Evaluation of gamified in uncontrolled environment

Phase 3 comprises a noninferiority, investigator-blinded, randomized clinical trial with two distinct groups: the intervention and control groups. Participants within the intervention group (IG) will install the gamified application on their smartphones and use a biosensor during exercise sessions. These sessions will align with the prescribed intensity derived from the ISWT, following the 6-week regimen detailed in phase 2. Participants will be duly instructed to cease exercising if they experience symptoms like chest pain, discomfort, or dizziness.

Within the gamified application, participants will have access to a diary feature, enabling them to log notifications received and their efforts during exercise, both monitored by the biosensor and the gamified app. On the other hand, individuals in the control group (CG) will receive instructions to engage in physical activity at home without biosensor monitoring. They will use the app independently, aiming for a minimum of 300 min per week at moderate intensity or at least 150 min per week at vigorous intensity (self-assessed).

Preceding and following the 6-week period, both the IG and CG will undergo assessments akin to those conducted in phase 1. These include evaluations of functional capacity, muscle oxygenation, and further assessments led by trained and blinded researchers.

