### Outcomes {12}

Primary outcomes will encompass the following: (1) the concordance between HR and step count measurements assessed by the biosensor under test compared to standard devices (Polar H10 and ActiGraph, respectively); (2) participant perception regarding the utility of the gamified application for exercise engagement; (3) comparison with the prevalence of adherence to the physical activity protocol between the control and intervention groups; (4) evaluation of exercise capacity through ISWT, including stage and the corresponding phase at which the test was halted; and (5) measurement of oxygen consumption (VO_2_).

Secondary outcomes will include the following: (1) tissue oxygenation assessed via near-infrared spectroscopy (NIRS), (2) subjective perception of exertion during ISWT, (3) evaluation of endothelial function, and (4) assessment of autonomic function.

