### Sample size {14}

Since phases 1 and 2 consist of a pilot study for the clinical evaluation of a biosensor prototype and the gamified application that considers a biofeedback system for performing physical exercises, a convenience sample of 15 individuals without medical contraindications for PA will be studied. Assuming a sample loss of 30%, we will recruit 20 participants.

The third phase will be a noninferiority, investigator-blinded randomized clinical trial of the individuals eligible for the study—considering the same eligibility criteria as in phases 1 and 2, in addition to being sedentary—will be divided into two groups: the intervention group (IG), which will receive the exercise protocol through the biosensor and gamified application, and the control group (CG), which will only receive guidelines for performing PA. Considering a confidence level of 95%, power of 80%, ratio of 1:1 between the CG and IG, and estimated prevalence of adherence to the protocol of 70% and 50% for the IG and CG, respectively, it would be necessary to allocate 104 individuals in each group. Adding 30% for possible follow-up losses, 149 sedentary individuals will be assigned to each group, totalling 298 subjects in the study.

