For the progression of our study through its phases, we have set clear criteria to determine the acceptability of outcomes: *Phase 1*: We regard the study as satisfactory if the standard error between the biosensor under test and the reference measurements is within 5%. If this criterion is not met, we would reconsider moving to the next phase until the discrepancies are addressed. *Phase 2*: The study’s progression will depend on the functionality of the application. Should there be serious errors within the application that prevent exercise or significantly hinder adherence, we would need to address these issues before considering progression to phase 3. *Phase 3*: Here, our benchmark for continuation is achieving at least 70% adherence. Any value below this would prompt us to assess the reasons for the reduced adherence and potentially re-evaluate our approach. Additionally, it is important to note that throughout all phases, we have ensured that there are no operational issues related to the app. Thus, significant data recording failures in earlier phases would indeed influence our decision to proceed to the next phase.

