### Gamification’s role in promoting PA

Gamification interventions have shown potential in boosting PA participation and self-monitoring while also promoting a sense of enjoyment. However, the literature lacks exploration of the impact of combining gamification with wearable activity devices for promoting PA, as evidenced by divergent findings from a recent systematic review [16]. This study aims to address this gap by investigating the effects of this combination. The hypothesis is that merging gamification with wearable devices can lead to improved adherence to exercise routines.

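### Phase 3 is declared a noninferiority trial without a margin or confidence-bound rule, while its sample size and hypothesis are those of a superiority trial on adherence

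*Protocol article*

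**What the plan says.** **The label.** The abstract (Methods) says "Phase 3 involves an investigator-blinded, randomized clinical trial to demonstrate noninferiority". Trial design {8} and the phase 3 description repeat the label: "Phase 3 comprises a noninferiority, investigator-blinded, randomized clinical trial with two distinct groups". So does Sample size {14}: "The third phase will be a noninferiority, investigator-blinded randomized clinical trial".

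**The sizing.** Sample size {14} takes 95% confidence, 80% power and equal allocation. The effect it assumes is an "estimated prevalence of adherence to the protocol of 70% and 50% for the IG and CG, respectively". The result is 104 per group, raised to 149 per group (298 in total) for 30% losses.

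**The aim.** The Discussion states "The hypothesis is that merging gamification with wearable devices can lead to improved adherence to exercise routines". Objectives {7} and the section on gamification's evolving role in health care point the same way, towards higher adherence.

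**The outcome and criterion.** Among the primary outcomes is "comparison with the prevalence of adherence to the physical activity protocol between the control and intervention groups". Section {20a} classes a participant as adherent at 70% completion of the prescribed protocol and sets significance at p < 0.05. Section {20c} plans intention-to-treat analysis of the primary outcomes.

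**A further benchmark.** The progression criteria in {20a} say of phase 3 that "our benchmark for continuation is achieving at least 70% adherence".

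**The comparator.** The abstract and Sample size {14} describe a control group that receives guidance only. The phase 3 description says that control participants use the app on their own, without the biosensor.

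**The concern.** A noninferiority trial is defined by its margin: the conclusion is drawn by comparing one confidence limit with that margin, and the sample size depends on it. Here the label appears in four places and the margin in none. Everything else in the design (rates, hypothesis, significance criterion) belongs to a superiority comparison.

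Two things are at stake. First, with a noninferiority label and only p < 0.05 to apply, a non-significant difference could be reported as showing noninferiority, which it does not. A margin chosen after the data are seen would not be credible. Second, a real adherence benefit would be reported under a framework that does not match the question. Showing that the intervention is not much worse than guidance alone does not show that it raises adherence.

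**Working it through.** **Inputs from Sample size {14}:** intervention 0.70, control 0.50, 95% confidence, 80% power, ratio 1:1, losses 30%. Sidedness is not stated.

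**1. Reproducing the plan's figure as two-sided superiority.** With mean rate 0.60:

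n = [1.96·√(2·0.60·0.40) + 0.8416·√(0.70·0.30 + 0.50·0.50)]² / 0.20² = (1.3579 + 0.5708)² / 0.04 = 93.0

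With continuity correction: (93.0/4)·[1 + √(1 + 4/(93.0·0.20))]² = 102.8, so 103 per arm. The plan says 104. One-sided versions give 74 (uncorrected) and 83 (corrected), which do not fit. For losses, 104/0.70 = 148.6, so 149 per arm and 298 in total, exactly as stated.

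The listed inputs thus yield the stated number, to within one participant, with no margin involved.

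**2. What a noninferiority calculation would give.** The margins Δ are my assumptions, since the document has none; one-sided 2.5%, 80% power:

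n = (1.96 + 0.8416)²·[p_I(1−p_I) + p_C(1−p_C)] / (p_I − p_C + Δ)²

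| True adherence (IG / CG) | Δ = 5 points | 10 | 15 | 20 |
|---|---|---|---|---|
| 70% / 50% (the plan's rates) | 58 | 41 | 30 | 23 |
| 50% / 50% | 1570 | 393 | 175 | 99 |
| 70% / 70% | 1319 | 330 | 147 | 83 |

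None equals 104. The nearest, 99, needs equal true rates and a 20-point margin, and the plan states neither.

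**3. Power of 104 per arm under each reading.**
- Superiority at 70% against 50%: 84% (uncorrected test).
- Noninferiority at the plan's own rates: SE = √(0.46/104) = 0.0665. For a 5-point margin, Φ(0.25/0.0665 − 1.96) = Φ(1.80) = 96%; for 10 points, over 99%.
- Noninferiority only if true adherence is equal in both arms (50% to 70%): 30–35% at 10 points, 58–66% at 15 and 82–88% at 20. About 18 to 19 points would be needed for 80%.

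**4. Cost of reading a non-significant result as noninferior.** Suppose the intervention is truly worse, 40% against 50%, with 104 per arm:

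- SE under no difference = √(2·0.45·0.55/104) = 0.0690
- SE under the alternative = √((0.24 + 0.25)/104) = 0.0686
- P(p < 0.05) = Φ((0.10 − 1.96·0.0690)/0.0686) = Φ(−0.513) = 0.304; the opposite tail adds less than 0.001
- P(p > 0.05) = 0.696

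With 149 per arm the SEs are 0.0576 and 0.0573, and P(p > 0.05) = 1 − Φ(−0.226) = 0.59.

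**5. The 70% benchmark.** If intervention-arm adherence is truly 70%, the chance that the observed proportion reaches 70% is P(X ≥ 73 | 104, 0.70) = 0.53, or P(X ≥ 105 | 149, 0.70) = 0.49.

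**The case against.** **The margin may sit in an analysis plan or full protocol that is not shown.** An article may leave out detail, but this is not an omitted detail. The sample size section lists its inputs under the noninferiority label, and those inputs give the stated number through a superiority formula. A later document cannot supply an input that this calculation did not use.

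**The ingredients of a superiority test are present.** This stands. A reader might infer that phase 3 has no valid decision rule of any kind. That goes too far: 95% confidence, p < 0.05, an adherence definition and intention-to-treat analysis could serve a superiority test. Only the declared noninferiority objective is without a rule.

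**The trial is large enough under either framework on its own assumptions.** This also stands. A reader might infer from the 30–35% power at a 10-point margin that phase 3 is underpowered. That figure holds only if true adherence is equal; at the plan's 70% and 50% the noninferiority power is about 96% even at 5 points.

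**No section says that a non-significant result will count as noninferior.** True, so the 70% in step 4 is conditional on that reading.

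**Five outcomes are called primary.** A reader might infer several between-arm tests and an inflated familywise error. The document does not support this: {20a} plans exercise capacity and VO2 as paired pre/post comparisons, and the five outcomes span all three phases.

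**The 70% benchmark is not an efficacy rule.** Fair: falling short prompts the team to look for reasons. A reader might also apply it to both arms combined, but the text states no such denominator.

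**Conclusion.** The contradiction is real and lies within the current text. Phase 3 is declared noninferiority, with no margin and no confidence-bound rule, while the sample size (103 reproduced, 104 stated) and the hypothesis are those of a two-sided superiority comparison of adherence. The arithmetic of 104 and 149 is sound; the label is what does not fit.

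If non-significance were taken as noninferiority, an intervention 10 points worse would pass about 70% of the time with 104 per arm and about 59% with 149. This rests on an assumed 40% against 50% and on a reading that the document leaves open but does not state. All noninferiority sample sizes and power figures rest on margins that I assumed.

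Two related matters need settling with it. The arm to which the 70% benchmark applies is not stated, and the intervention arm alone would reach it only about half the time at its planned rate. The sections on what the control group receives also disagree, so the contrast being tested is not fully defined. Because the trial's main conclusion depends on the choice of framework, this must be fixed before phase 3 is analysed.

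**What to change.** 1. Delete noninferiority from the abstract, Trial design {8}, the phase 3 description and Sample size {14}, and call phase 3 a superiority trial.
2. Name the intervention-minus-control difference in the proportion adherent as the confirmatory phase 3 comparison, with a 95% confidence interval, two-sided 5% level and intention-to-treat analysis. It is the only outcome that is sized.
3. State that the 70% figure in the progression criteria is a feasibility benchmark, say to which arm it applies, and say that it is not a success criterion for the between-arm comparison.
4. Reconcile the sections on whether control participants use the app or receive guidance only, so that the contrast is defined.

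The cost is protocol and registry wording. The sample size stays at 104 per arm, 149 after losses.

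If noninferiority is truly intended, state and justify a margin and a confidence-bound rule before any phase 3 data are seen, and recompute the sample size. Depending on the margin and the assumed true rates, the table above shows that the number could fall well below or rise far above 104.
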